**4.0 INTERVENTIONS**

(1) Health facility based IPTc: Community mobilisation and education on IPTc offered at the EPI/growth monitoring clinic will be carried out. The IPTc drugs will be delivered at all (both static and out reach) EPI/growth monitoring clinics.

(2) Community based IPTc: A network of community volunteers (Mother co-ordinators) will be identified and trained. The IPTc drugs will be delivered every month to these volunteers by the district EPI nurse and the volunteers deliver the drug to the children in their respective villages.

**5.0 TRIAL END-POINT**

**5.1 Primary end –point**

1. The proportion of children receiving the full course of IPTc (four courses) during the rainy season.

**5.2 Secondary end-points:**

1. Proportion of IPTc courses completed per protocol (adherence to treatment regime)
2. Incidence of clinical malaria
3. Prevalence of malaria parasitaemia at the end of the rainy season.

## 6. STUDY SITE AND POPULATION

**6.1 Study Area**

The study will be carried out in the Jasikan district of Ghana. This is in the northern part of the Volta Region. It is bounded by the Togo-Ghana mountain ranges to the east, Kpando and Hohoe Districts to the south, Kadjebi District to the north and the Volta Lake to the west. The population of Jasikan district in 2004 was estimated to be 122,265. Most of the residents are subsistence farmers who grow rice and maize. The District falls within the semi-equatorial climatic zone and has an extended rainy season (May – November) with peaks in June-July and September- October. Malaria transmission peaks from May to October. *P. falciparum* is the dominant species, being responsible for all severe diseases and over 98% of clinical attacks. A few cases of clinical malaria are caused by *P.* *malariae*. In rural areas, children experience 3-6 clinical attacks of malaria a year. Over 70% of clinical attacks occur during the rainy season. Severe malaria is the most common cause of admission and death in children under five years (Jasikan district annual report 2004). Volta Region has relatively good coverage with EPI vaccines; over 80% of one year olds received the full range of vaccines according to the 2003 DHS.

**6.2 Health facility in the study area**

There are eight health centres and two hospitals in the district. Each health centre has a resident nurse or Medical Assistant. Jasikan district hospital owned by Ghana Health Service (GHS) and Worawora hospital owned by mission serve as referral hospitals. Worawora hospital has a 120 in-patient bed facilities while Jasikan district hospital has 40. Each hospital has a resident doctor.

**7.0 STUDY DESIGN AND METHODOLOGY**

**7.1 Trial Design**:

An open label trial with two arms: (1) Health facility based IPTc; (2) community based IPTc. Children in both arms will receive four courses of AQ+SP (a three day regime) in May, June, September and October (Figure 1). The EPI nurses will collect drugs from the District Health Directorate (DHD) when collecting vaccines and family planning devices for their outreach activities. The nurses will transport and deliver the drugs to the health centre staff and community-based IPTc coordinators in their catchment areas for distribution. They will also carry out health education activities about IPTc during child welfare clinics in the communities. The schedule for drug administration and number of doses per child in a year will be designed in the child’s road to health card. EPI nurses will pass on information through mothers/guardians who attend child welfare clinics or through their routine contact persons in the communities on scheduled days for drug distribution.

**Figure 1. Structure of IPTc delivery systems**

Health centre

Nurse in charge

EPI nurse

DHMT

1. Distinct Director of Health services

2. IPTc coordinator (Disease control office/Public health nurse

Mother coordinators

Deliver IPTc in the villages

Health centre and EPI/Growth monitoring staff

Deliver IPTc at EPI/growth monitoring clinics at the health centre

**7.2 Screening for eligibility**

Children whose parents or guardians wanted their wards to participate will be assessed by the research team for eligibility for enrolment into the study: Children with the following conditions will be excluded from the study: (1) severe malnutrition; (2) chronic diarrhoea; (3) history of convulsions; (4) prostration, extreme weakness (inability to stand or sit); (5) history of hypersensitivity to AQ or SP. The study staff will examine the children for these criteria at the time of pre intervention cross sectional survey and refer children having any of these conditions to the PI for the final decision.

**7.3 Obtaining informed consent**

This process will be carried out by trained field supervisors and fieldworkers using the local language Ewe, Buem and Akan in the district. All parents and care takers who will consent to participate will append their signature or right thumb print on two copies of the consent form in the presence of a witness (non-study related person) who also will sign or affix his/her thumbprint. The field supervisor/worker will also sign to indicate that (s)he has adequately informed the participant about the study and answered all questions.

**7.4 Sample size**

The sample size calculation for the primary end-point takes into account that the village and not the individual, is the unit of randomization. The number of villages required for the trial depends on the expected compliances in the village based and health centre based delivery systems, the variability in compliance between villages and the number of participating children in each village. Assuming 80% compliance in the community based IPTc delivery system and 45% or worse compliance in health centre based delivery system with a coefficient of variation between villages of 0.25, assuming that there are 60-100 children in each village, 5 villages or cluster of villages in each arm will be needed for the study. Such a study will have 80% power at 5% level of significance to show a difference in compliance.

All children eligible and their parents consented to participate in the study will be recruited. The recruited children (600-1000) will be included in the cross-sectional surveys at the beginning and end of the intervention.

**7. 5 Enumeration, recruitment and consent**

Five villages with an average population of 80 children aged less than five years will be allocated to receive IPTc distributed by health staff from five health centres. Five villages of the same size will be selected to receive IPTc from a community-based IPTc coordinator.

Once villages have been chosen in April 2006, several meetings with all potential partners (health authorities, community leaders and care givers) will be held. Meetings will be held with the district health directorate staff and assembly members from the district administration. We will then hold meetings with the chiefs and elders, opinion leaders and parents or guardians of prospective study subjects in the villages selected. Explanations will be provided to opinion leaders and parents in local languages, emphasising the potential public health impact of the study for malaria control. They will be provided with information sheets in English or in the appropriate local language (Ewe or Akan).

Enumeration of all children aged between 3-59months of age in the study area will be carried out in April 2006 and a database established before the start of the study.

Approximately, 960 children will be eligible for enrolment in the study. Enrolled subjects will be provided with an identification card on which their names, age, sex, weight at enrolment, drug code mother/guardian’s name and study number will be written to facilitate identification at each contact.

**7.6 Training of drug distributors**

The community-based IPTc coordinators will be selected in consultation with the villagers and they will receive training on how and when to administer IPTc drugs to children and how to complete the tally sheets, adverse event forms and keep records of all deaths in the study children during the period of intervention. The training will also highlight the importance of their role in the study and how it relates to that of others. At the training, they will be encouraged to do their best to ensure high quality work. The health centre distributors will be identified by the District Health Management Team and they will also receive training as above.

**7.7 Cross-sectional surveys**

Two cross-sectional surveys will be undertaken in May and November 2006. The first survey will be the pre-intervention survey which will provide baseline information about the study children and the second one will be a post- intervention survey. In both surveys, information to be collected will include the background information about the child and mother/guardian, history of allergy to any of the study drugs, bednet ownership and use, measurement of temperature and anthropometric indices. This will also involve collection of finger prick blood samples for determination of asexual and sexual parasitaemia.

**7.8, Drug administration and Follow-up:**

Drug administration to the study children will start in June 2006. The IPTc coordinators will distribute the trial medication at a central point in the village, while the health staff will do the distribution at a convenient place in the health centre. Two consecutive days will be allowed for drug distribution within the week in which drugs are received. A convenient day to start will be chosen by the parents of the participants. The first dose will be given under direct supervision of the distributors and the subsequent doses for day 2 and 3 will be given to the mothers/guardians to administer at home.

Adherence in the facility based IPTc arm will be assessed on a rolling basis throughout the study by assessing the number of courses received and correct doses of medication administered. Four days after the first dose was administered field workers will visit every village and health facility to collect drug distribution forms. They will also visit some randomly computer generated selected mothers at home to check for left over medication and ask for any side effects after the first dose of drug administration.

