**3.0 STUDY OBJECTIVES**

- 1. **Primary objective**

To compare the coverage of IPTc achieved through two different delivery systems.

- 1. **Secondary Objective**

To compare the level of adherence to the IPTc regime in the two delivery systems

To assess the impact of IPTc on the incidence of malaria

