**November 006**

Post intervention prevalence of malaria and coverage of IPTc measured.

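### A rolling check of courses received and correct doses is written for the facility arm only: an extra, unmatched assessment in an open-label comparison of the two arms

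*Protocol*

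**What the plan says.** Section 3.0 sets a between-arm adherence objective: "To compare the level of adherence to the IPTc regime in the two delivery systems". Section 5.1 makes the primary endpoint the proportion of children who receive all four courses. Section 5.2 lists the proportion of courses completed per protocol as the adherence endpoint. Section 7.1 describes the trial as open label.

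On how these are observed, section 7.8 states: "Adherence in the facility based IPTc arm will be assessed on a rolling basis throughout the study by assessing the number of courses received", together with whether the medication doses were correct. The sentence names the facility arm and has no counterpart for the community arm anywhere in the protocol.

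The text that follows in 7.8 is not limited to one arm. Four days after the first dose, "field workers will visit every village and health facility to collect drug distribution forms". Of the same field workers it says: "They will also visit some randomly computer generated selected mothers at home to check for left over medication".

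Section 7.6 trains community distributors in "how to complete the tally sheets, adverse event forms and keep records of all deaths in the study children", and gives health centre distributors the same training. The Timetable entry for November 2006 reads: "Post intervention prevalence of malaria and coverage of IPTc measured". For the two surveys, section 7.7 says that "information to be collected will include the background information about the child and mother/guardian", followed by allergy history, bednets, temperature, anthropometry and a blood sample. Courses received are not named there.

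**The concern.** In an open-label trial that compares two groups of distributors, the outcome should be observed in the same way and equally often in both arms. The rolling assessment covers the number of courses received, which is the variable behind the primary endpoint, and correct dosing, which bears on adherence. Staff who follow 7.8 as written would look at these continuously in one arm only.

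The effect could run either way. A continuous check may disqualify facility courses or doses that would stand unchallenged in the community arm. It may also pick up facility courses that the forms left out, or prompt better delivery and uptake where staff know they are being watched. More children would not remove such a difference. An analysis plan can choose among data sources, but it cannot supply observations that were never made in one arm.

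**Working it through.** **Step 1. Sources of data on courses and doses, by arm**

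| Source | Place in protocol | Facility arm | Community arm | What it yields |
|---|---|---|---|---|
| Rolling assessment | 7.8 | yes | not stated | courses received, correct doses |
| Distribution forms | 7.8 | yes | yes | distributors' record of each round |
| Home visits to randomly selected mothers | 7.8 | yes, share not stated | yes, share not stated | leftover medication, side effects |
| ID card | Appendix 3 | yes | yes | four administration dates |
| Supervision form | Appendix 4 | yes | yes | distributor conduct, including dosage and marking the card |
| Monitoring form | Appendix 9 | yes | yes | completion of the three days of a course |
| November measurement | Summary, Timetable | yes | yes | coverage, with no arm restriction |

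Only the first row differs between arms. For course receipt, the ID card and the November measurement offer a common route. For adherence the shared material is thinner. The home visits reach only some mothers, the monitoring form covers the days within a course, and the supervision form describes the distributor and not each child. The mismatch therefore matters more for adherence than for the primary endpoint.

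**Step 2. The plan's own figure**

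Inputs from section 7.4: p1 = 0.80 (community), p0 = 0.45 (facility), between-village coefficient of variation k = 0.25, m = 60 to 100 children per village, 80% power, 5% level (two-sided assumed). The Hayes-Bennett formula for unmatched clusters is

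c = 1 + (1.96 + 0.84)² × V / (p1 − p0)², with V = p0(1 − p0)/m + p1(1 − p1)/m + k²(p0² + p1²).

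At m = 80: V = 0.2475/80 + 0.16/80 + 0.0625 × 0.8425 = 0.0578, and c = 1 + 7.85 × 0.0578/0.1225 = 4.70. At m = 60 and m = 100, c is 4.81 and 4.63. Each rounds up to the stated 5 per arm, so the sample size reproduces and is not in question. Power with 5 per arm, Φ(√[4(p1 − p0)²/V] − 1.96), is 81.9% to 83.6%, and 83% at m = 80.

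**Step 3. What unequal counting could do (assumed shares)**

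The documents give no recording-error rate. Assume that a share s of the children who would count as completers under a common procedure is not counted in one arm. The uncounted arm's proportion becomes p × (1 − s). With m = 80 and 5 villages per arm:

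| s | Missed in community arm: difference | Power | Missed in facility arm: difference |
|---|---|---|---|
| 0% | 80 − 45 = 35 points | 83% | 35 points |
| 5% | 76 − 45 = 31 points | 76% | 80 − 42.75 = about 37 points |
| 10% | 72 − 45 = 27 points | 67% | 80 − 40.5 = about 40 points |
| 20% | 64 − 45 = 19 points | 44% | 80 − 36 = 44 points |

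The table shows sensitivity only. It uses the primary endpoint's planning values because the protocol gives none for adherence.

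**The case against.** The strongest reply is that the protocol already observes both arms through common instruments, and that one phrase in 7.8 is probably a drafting slip, since the form collection described next covers every village and facility. The first half stands, and it rules out several stronger readings that a reader might infer.

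- *That only the facility arm is audited.* Appendix 4 carries a delivery-system field and records, for either kind of distributor, whether the dose was right, the administration form completed and the ID card marked. The budget funds supervisors for the community coordinators. Section 7.8 names no assessor for the rolling check and does not say that it corrects records.
- *That distributors' own records are the only complete source for the primary endpoint.* The Summary and Timetable place outcome and coverage measurement in the surveys, without arm restriction. The list in 7.7 is open-ended and describes items common to both surveys. Course receipt could not be collected at a pre-intervention survey, so its absence from a common list is not a contradiction. The material between Appendix 4 and Appendix 6 was not available for this review, so the set of forms is not fully visible.
- *That the bias can be quantified.* One could compound an assumed per-course recording error over four courses and reach a shift close to the planned difference. Any such figure depends on the error rate chosen, and the protocol states neither a rate nor a direction.

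The drafting-slip argument does not remove the point. Field staff act on the text, and the text directs the check to one arm. Procedures (SOPs) or an analysis plan may hold further detail, but they would have to go beyond what 7.8 says.

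**Conclusion.** The point holds in a limited form. Section 7.8 specifies an additional assessment of courses and doses in the facility arm that is not matched in the community arm, while both outcomes are compared between arms without blinding. It could bias the adherence comparison and, less strongly, course receipt. Neither size nor direction can be derived from the documents. The range in the working rests on assumed shares of uncounted completers, with the planning values of section 7.4 and 80 children per village. The reading of the text is firm; the consequence is a possibility. The severity is that of a clarification worth making before the first distribution round, below a mandatory correction.

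**What to change.** In 7.8, replace the words that confine the rolling assessment to the facility arm with: in both arms, using the same forms and timing.

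In 7.7, add that in the November survey the survey staff, not the distributors, record for every enrolled child in both arms the four dates on the ID card and the caregiver's report of courses taken. State that this is the common source for the primary endpoint, with the distribution forms as a cross-check.

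The cost is slightly more time per child in a survey that is already planned, and the same rolling check in community villages that field workers already visit. The card already has the four date fields. No dose or clinical rule changes. The change is needed before distribution begins, because observations not made during the rounds cannot be reliably recovered later.

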**Appendix 9**

### Jasikan IPTc delivery system study

### Monitoring form

Community……………………………………………………..Date------/-------/2006

Child’s first name…………………………………..Last name………………………...

Date of birth -----/------/--------Child’s ID Number [ ] Delivery system [ ]

Mother/guardian’s First name…………………………Last name……………………

Age[ ] Educational level…………………………Occupation……………………..

Noticed any adverse event during drug administration[Y] [N]

If yes,

| Adverse event | Date onset | Time onset | End date | End time | Severity[[1]](#footnote-2)1 |
| --- | --- | --- | --- | --- | --- |
|  |  |  |  |  |  |
|  |  |  |  |  |  |
|  |  |  |  |  |  |

| Indicator | Circle Y or N |
| --- | --- |
| Own bednet | [Y] [N] |
| If yes since when did you get the net |  |
| If YES has net been treated within the past 12 months | [Y] [N] |
| How much did you pay for the net | **¢** |
| Did child sleep under net last night | [Y] [N |
| Look at the net | [Y] [N] |
| Brand of net (the label on the net) |  |
| Did the child complete the three doses of IPTc drugs (For 3 days?) | [Y] [N] |
| If no how many doses (days) completed | [ ] |
| Child vomited drug at home | [Y] [N] |
| If yes Action taken (collect extra dose and repeated) | [Y] [N] |

1. 1 Severity: 1=Mild, 2=Moderate, 3=Severe [↑](#footnote-ref-2)

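### Section 7.8 assesses adherence by courses received, and for the facility arm only, while section 5.2 defines it as courses completed; the home-visit data that could measure completion are not tied to the endpoint

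*Protocol*

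**What the plan says.** Section 3.0 has coverage as the primary objective and, as a separate secondary objective, a comparison of adherence in the two delivery systems. The endpoints follow that split. The primary endpoint (5.1) is "The proportion of children receiving the full course of IPTc (four courses) during the rainy season". The first secondary endpoint (5.2) is "Proportion of IPTc courses completed per protocol (adherence to treatment regime". Sections 7.1 and 7.10 make each course three days long.

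Section 7.8 describes the field procedure. The first dose is supervised by the distributor, and "the subsequent doses for day 2 and 3 will be given to the mothers/guardians to administer at home". On adherence it states: "Adherence in the facility based IPTc arm will be assessed on a rolling basis throughout the study", and this is done "by assessing the number of courses received and correct doses of medication administered". It then says that four days after the first dose field workers will "visit some randomly computer generated selected mothers at home to check for left over medication". The Appendix 9 monitoring form asks "Did the child complete the three doses of IPTc drugs (For 3 days" and, for incomplete courses, "If no how many doses (days) completed". It also has a field for delivery system.

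**The concern.** The endpoint and the stated way of assessing it do not match, in two respects.

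- **Completion against receipt.** Section 5.2 counts courses completed. Section 7.8 counts courses received, plus correct doses administered. Receipt is what 5.1 already counts, so an adherence measure built on it carries the coverage difference into the adherence comparison.
- **One arm against two.** The secondary objective compares two delivery systems, but the adherence sentence in 7.8 covers the facility arm alone. No corresponding rule is given for the community arm.

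The information needed to measure completion is planned, but nothing says that it feeds the 5.2 endpoint. At stake is whether the trial can say anything about adherence beyond its coverage result.

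**Working it through.** **The texts side by side**

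- 5.1: counts children; the event is receipt of all four courses.
- 5.2: counts courses; the event is completion per protocol. It does not say whether the denominator is courses scheduled or courses received.
- 7.8, adherence sentence: courses received and correct doses administered; facility arm; no denominator.
- 7.8, home visits: left-over drug four days after the first dose, in a random sample of mothers; not restricted to one arm; sample size not stated.
- Appendix 9: three-day completion yes/no, and days completed if not; delivery system recorded.
- Appendix 4 (supervision form): whether the doses for days 2 and 3 were packed correctly, which does not show that they were taken.

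Only the home visits and Appendix 9 bear directly on completion at home.

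**The plan's own figure.** The protocol gives no figure for adherence. Its sample size (7.4) reproduces with c = 1 + (1.96 + 0.84)² × [p0(1−p0)/m + p1(1−p1)/m + k²(p0² + p1²)] / (p1−p0)². Inputs are p1 = 0.80, p0 = 0.45 and k = 0.25, with a two-sided 5% level assumed. For m = 60, 80 and 100 this gives c = 4.81, 4.70 and 4.63, so 5 villages per arm. The present point does not change that number.

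**Illustration of the overlap with coverage**

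Inputs: 80% and 45% from 7.4, taken here as four-course receipt. Assumptions not in the protocol: the four courses are received independently, and home completion h is the same in both arms, at 70%, 80% or 90%.

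1. Per-course receipt: r1 = 0.80^(1/4) = 0.946 (community); r0 = 0.45^(1/4) = 0.819 (facility).
2. Courses received over scheduled: r1 − r0 = 0.127, whatever h is.
3. Completed over scheduled: h × (r1 − r0) = 0.089, 0.101 and 0.114 for h = 0.7, 0.8 and 0.9.
4. Completed over received: h − h = 0.

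| Measure | h = 70% | h = 80% | h = 90% |
| --- | --- | --- | --- |
| Received / scheduled (points) | 12.7 | 12.7 | 12.7 |
| Completed / scheduled (points) | 8.9 | 10.1 | 11.4 |
| Completed / received (points) | 0 | 0 | 0 |

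With identical behaviour at home, the first two measures still show an arm difference that comes entirely from coverage. Only the third does not.

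**The case against.** The strongest reply is that 7.8 describes fieldwork, 5.2 defines the endpoint, and the denominator, source form and handling of a subsample are normally left to a statistical analysis plan, which is not shown. That stands for those details. It does not cover a sentence that names a different measure for the same endpoint and limits it to one arm.

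Several stronger readings are tempting, and the documents do not support them.

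- *That doses on days 2 and 3 go unchecked.* They are checked, by the left-over visits in 7.8 and the completion items in Appendix 9. What is missing is the link to the endpoint.
- *That a child who takes day 1 and discards the rest is adherent under 7.8.* That holds only if doses administered means doses seen by the distributor. The same section uses the verb for doses given at home, so the wording is ambiguous rather than clearly wrong.
- *That 7.8 counts over courses offered, so its denominator contradicts Appendix 9.* Section 7.8 states no denominator.
- *That 5.2 already fixes completed over received.* It does not; completed over scheduled fits its words equally well, and that version keeps part of the coverage difference.
- *That adherence would be reported in the wrong direction.* With assumed home completion of 80% community v 90% facility, receipt gives +13 points and completed over received −10. But that needs both the assumed deficit and a receipt-only reading of 7.8 applied to both arms, and 7.8 states neither.

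**Conclusion.** The point holds as an inconsistency between a defined secondary endpoint and its stated assessment. As written, 7.8 cannot deliver the comparison promised in section 3.0, because it covers one arm and includes receipt where 5.2 requires completion. To the extent that receipt drives the measure, it partly repeats the primary contrast.

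The size is illustrative: about 13 points as courses received, 9-11 as completed over scheduled, 0 as completed over received. It rests on independent courses, on reading 80% and 45% as four-course receipt (7.4 says only compliance), on equal home completion of 70-90%, and on a receipt-only measure in both arms. A reader might infer a spurious difference of up to 35 points (80 − 45). That would require receipt to be all-or-nothing for each child, or the two figures to be shares of courses, as well as the receipt-only reading; the protocol states none of these. The dependence on the definition does not rest on the particular values.

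The primary endpoint and the sample size are unaffected. This should be corrected, but it does not undermine the trial's main comparison.

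**What to change.** Rewrite the adherence sentence in 7.8:

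- Remove the restriction to the facility arm and the reference to the number of courses received.
- Assess adherence identically in both arms from the day-4 random home-visit sample, with the Appendix 9 three-day completion item as the numerator. State how many mothers are visited per village and round.
- State the denominator as courses received, and say that this is a choice which 5.2 leaves open. Label the comparison as conditional on receipt.
- Give completed over scheduled courses as a supportive figure.
- Report courses received under coverage only.

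The cost is mainly wording, since the visits and the form already exist. The downside is that adherence is estimated in a subsample and only among recipients, so it is less precise than a count over all children and says nothing about those who received no course. The loss of precision cannot be quantified from the protocol, because the visit sample size is not given.

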**7.11 Assessment of adverse Events**

***Eliciting and documenting adverse experiences***

All adverse events or reactions, which occur during the trial, will be documented. The nature of each experience, date and time (where appropriate) of onset, duration, severity and relationship to treatment will be established whenever possible.

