**Appendix 6**

### Jasikan IPTc delivery system study

### Adverse event reporting form

Community ………………….

Child’s First Name………………………… Last name……………………..

Child’s ID Number: |___|___|___|___|___|

Mother’s First name……………………………Last name…..……………….

**Notified adverse events** [Y] [N]

If yes,

| Adverse event | Date onset | Time onset | End date | End time | Severity |
| --- | --- | --- | --- | --- | --- |
| General bodily weakness |  |  |  |  |  |
| drowsiness |  |  |  |  |  |
| Difficulty in breathing |  |  |  |  |  |
| Vomiting |  |  |  |  |  |
| Cannot sleep |  |  |  |  |  |
| Cannot eat |  |  |  |  |  |
| Other |  |  |  |  |  |
| Other |  |  |  |  |  |
| Other |  |  |  |  |  |

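### Section 7.11 promises that every adverse event will be documented, but the only scheduled enquiry described is a day-4 visit to an unspecified sample of mothers, with a loosely worded question

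*Protocol*

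**What the plan says.** Section 7.11, on eliciting and documenting adverse experiences, states: "All adverse events or reactions, which occur during the trial, will be documented". The next sentence lists the details wanted for each event and ends: "duration, severity and relationship to treatment will be established whenever possible". That qualifier applies to the details, not to whether an event is recorded.

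Section 7.8 describes the scheduled contact. "Four days after the first dose was administered field workers will visit every village and health facility to collect drug distribution forms". They are also to "visit some randomly computer generated selected mothers at home to check for left over medication and ask for any side effects after the first dose". The same section leaves the day 2 and day 3 doses to the mother or guardian at home.

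Two forms bear on this. The monitoring form (Appendix 9) puts its event question as "Noticed any adverse event during drug administration". The adverse event reporting form (Appendix 6) has the columns "Adverse event | Date onset | Time onset | End date | End time | Severity".

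Other routes exist. Distributors in both arms are trained to complete adverse event forms (Section 7.6). Parents are advised to attend a health centre for any sign of illness, and admissions and deaths are recorded (Section 7.9). The outpatient and inpatient forms (Appendices 7 and 8) include vomiting, itching, jaundice, mouth sores and rash.

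**The concern.** The promise is universal and the procedure is a sample. Nothing described has every caregiver asked about adverse events, although returning children are seen at each later course and all recruited children are to be surveyed at the end (Section 7.4).

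Two things are at stake. The first is safety. The DSMB is to review and analyse the clinical safety data. It would receive events from a sample of unknown size mixed with events that came to light because someone sought care or reported them. Without separate denominators, no rate can be read from that mixture.

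The second is interpretation of the primary endpoint, the proportion of children receiving all four courses. None of the forms shown has a place for the reason a course was missed. A family that stops after a reaction cannot be told apart from one that the delivery system failed to reach.

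**Working it through.** The protocol gives no figure to reproduce here, so the check is mainly a comparison of text, followed by an illustration.

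**1. Who is asked.** Section 7.11: all events. Section 7.8: some mothers, chosen at random, fraction not stated.

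**2. How often.** The visit is tied to collecting distribution forms after a first dose. With four courses it may recur each time, but Section 7.8 does not say so.

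**3. Whether the timing could cover the home doses.** Distribution is allowed on two consecutive days; call them day 0 and day 1, with the visit on day 4. A child dosed on day 0 has home doses on days 1 and 2. A child dosed on day 1 has them on days 2 and 3. In both cases the visit falls after the last home dose. The timing is adequate for the home doses, so the weakness lies in the wording.

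**4. What is asked.** Section 7.8 can mean effects of the first dose, or anything since it. Appendix 9 refers to events during administration. Read narrowly, both omit events in the hours or days after a home dose. Appendix 9 does ask whether three days were completed and whether the child vomited the drug at home, but those items cover only one kind of event.

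**5. What remains for other events.**
- Distributors are trained on the form, but no step tells them to ask at the next course. The supervision checklist in Appendix 4 has no such item.
- The surveillance in Section 7.9 is set up for malaria episodes.
- The collection rounds name distribution forms (7.8), record forms and slides from facilities, and forms on community deaths from coordinators (7.9). Retrieval of adverse event forms from coordinators is not named. This is one way in which capture could differ by arm.
- The November survey content (Section 7.7) lists drug allergy history but no general enquiry about events.

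**6. Relationship to treatment.** Section 7.11 wants it where possible; Appendix 6 has no field for it. The preceding course needs no new field, because Appendix 6 has the onset date and the ID card (Appendix 3) has the four administration dates.

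**7. Illustration.** Inputs: about 960 children (Section 7.5), 4 courses (Section 7.1), and a sampling fraction f that is *assumed* at 5% to 50% because the protocol gives none. Total child-courses = 960 × 4 = 3,840.

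| f (assumed) | Child-courses asked, every round (f × 3,840) | Asked, first round only (f × 960) | At least one of 5 affected children sampled, 1 − (1 − f)^5 |
|---|---|---|---|
| 5% | 192 (5%) | 48 (1.25%) | 0.23 |
| 10% | 384 (10%) | 96 (2.5%) | 0.41 |
| 25% | 960 (25%) | 240 (6.25%) | 0.76 |
| 50% | 1,920 (50%) | 480 (12.5%) | 0.97 |

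The percentages do not depend on the 960. The last column is for one round, with children sampled independently. The table concerns active enquiry only. Only f = 100% in every round would put the question to every child at every course.

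**The case against.** The strongest reply is that a sampled active enquiry backed by passive reporting is a reasonable design for a delivery pilot, and that the passive side is substantial: trained distributors in both arms, advice to attend for any symptom, clinic forms that list likely drug reactions, and records of admissions and deaths. This stands, and it rules out three stronger readings that a reader might draw.

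- *That mothers are asked only once.* The protocol does not say so; it is silent on repetition.
- *That events after the home doses are excluded.* The wording permits that reading but does not require it. The visit comes after those doses, and Appendix 9 has onset dates and asks about vomiting at home. No text expressly ties Appendix 9 to the day-4 visit either.
- *That most events would be missed.* The yield of the passive routes is unknown, so no missed share can be derived. The table above must not be read as one.

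It can also be said that both arms receive the same drugs, so refusal after a reaction has no built-in reason to favour one arm. That is fair, but such refusal would still lower coverage and be counted as a shortfall in delivery. Finally, the standard operating procedures and the material between Appendices 4 and 6 were not available to this review, so a rule for asking every caregiver might exist there. None is described in the protocol text that was.

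**Conclusion.** The point holds as a mismatch between Section 7.11 and the procedures meant to deliver it. The scheduled enquiry covers a sample of unstated size, with unstated repetition and ambiguous wording. Everything outside it rests on passive routes, and relationship to treatment has no place on the adverse event form. Capture is likely to be incomplete, tilted towards families who seek care, and possibly uneven between arms. The extent cannot be computed from the protocol. This does not invalidate the comparison of coverage. It weakens what can be said about safety and about why courses were missed, and it is worth correcting because the contacts needed already take place. The conclusion assumes that no unseen procedure already has every caregiver asked.

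**What to change.** 1. In Section 7.8 and Appendix 9, word the day-4 question as: *at any time since the first dose of this course, including the day 2 and day 3 doses*. State that the visit repeats at each course, and state the fraction sampled.
2. At courses 2 to 4 and at the November survey, ask every caregiver in both arms the same question about events since the previous course and the reason for any missed course. Record the answers on Appendix 6, with a line added for the reason.
3. Add a relationship-to-treatment field to Appendix 6, completed by clinical staff or the local safety monitor rather than by the distributor.
4. Report day-4 events with the sampled children as denominator, separately from passive reports, and limit the promise in Section 7.11 to events reported or elicited.

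The cost is changes to wording and forms, plus a minute or two per contact. Recall is the main limitation. With courses in June, July, September and October (Section 7.10), it is 1 to 2 months for returning children and about five months, June to November, for children who stopped after the first course. Section 7.1 lists May, June, September and October instead, which would lengthen these to as much as three and six months. The two schedules need to be reconciled in any case.
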